### Data Collection

All study data will be aggregated and analyzed at the end of the study period. Data will be collected at enrollment and closeout as described in  Multimedia Appendix 3. Patient demographics will be collected using an enrollment questionnaire developed by the study investigators. All data pertaining to health care utilization (emergency department visits, readmissions during study period, avoidable admissions, mortality, and total medical expenditures) will be extracted from the Partners Healthcare patient databases—Enterprise Data Warehouse and the Remote Patient Data Registry. The total cost of intervention provided to patients by PHH will be sourced from the PHH program costs. The emergency transport use data will be collected from the Phillips Lifeline database.

The Remote Patient Data Registry is a centralized clinical data warehouse that operates under Partners Research Information Services. It securely stores all data from across Partners hospital systems in one place and ensures security and confidentiality of patient information [16]. The Enterprise Data Warehouse is a single repository of clinical, operational, financial, and claims data of patients receiving care across the Partners system. The Phillips Lifeline database contains historical data such as demographics, patients’ living situations and care giver network, self-reported medical conditions, and emergency transport data from the PERS device. The care-giver network information includes number of responders, the number of people who live with the patients, and persons to be notified after an emergency transport. Emergency transport data from the PERS device includes all information gathered during the interactions of the patients with the Lifeline call center associates. For all calls, the situation (eg, fall, respiratory problems, chest pain, and social call) and the outcome (eg, subscriber OK, responder assistance, and emergency hospital transport) are collected by the associate via custom-made software. All other data collected via questionnaires is stored in a secure electronic database, REDCap, which is a secure Web application for building and managing Web-based surveys and databases.

Patients meeting the initial eligibility criteria are identified through an Enterprise Data Warehouse query. The query will be written in structured query language to identify patients who meet the pre-set criteria. PHH study staff acquire a daily list of medical record numbers of newly-admitted patients, and then run the query for that distinct list of patients. The query output summarizes the patients’ age, 2016 health care costs, and determines whether their health care costs place them in the middle cost acuity segment. Eligible patients will be contacted by study stuff to be enrolled into the study if interested.

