
Participants in the control group will receive the following:

Passive Monitoring: These participants will continue to use the PERS system. After the 3-month observation period, the CareSage algorithm will continue to only passively monitor control group participants but will not alert the study nurse about their risk for emergency transport. The data from CareSage will continue to be captured at the backend and will be collected at the end of the study.Care as usual: Participants will continue to receive medical treatment and discuss any questions or concerns with their care providers as usual. There will be no triage for control group participants.

Participants in the intervention group will receive the following:

Active monitoring: Patients in the intervention group will be assessed by the Web-based CareSage risk assessment system, which can identify when a patient is at risk for emergency transport in any upcoming 30-day period. Patients identified as “high risk” will receive nurse triage calls and, depending on their needs, tailored interventions per a stepped-care approach (Figure 2). The principal goals of the intervention will be to address knowledge gaps in disease self-management, ensure compliance with medications and healthy diet, and identify recurrent symptoms amenable to treatment on an outpatient basis to prevent readmissions.Nurse Triage Call*:* During the intervention period, “high-risk” patients will be called by a trained study nurse to assess the physical and psychological patient’s needs using a health needs assessment guide (Multimedia Appendix 2) developed by the study team. These 15-30-minute telephone calls will focus on how the patient is feeling, adherence to treatment plans, and connect the patient to any available resources (primary care physician, dietician etc) as needed.

Tailored PHH Interventions The PHH interventions consist of multiple components tailored to individual patients based on the needs identified during nurse triage call. The complete intervention decision pathway is depicted in Figure 3. There are 3 interventions that the study nurse may offer.

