#### Statistical Analysis Plan

Data collected will be analyzed with data analysis (STATA, version 14) and statistical software (R, version 3.4.1). All the analyses will be conducted per the intention-to-treat principle. Descriptive statistics will be used to characterize the study sample, and we will summarize participants’ characteristics by study arm. The two study groups (intervention and control) will be compared by the Student *t*-test (two-tailed) for normally distributed and the Mann Whitney *U* test for skewed continuous variables, respectively. The chi-square test will be used for categorical variables. Time to event (readmission) and 180-day mortality between the two study groups will be compared by using the Kaplan-Meier survival plots and the log-rank test. Cox proportional hazard regression will be used to compute hazard ratio and compare outcomes between the two groups. We will also conduct subgroup analyses based on enrollment in iCMP during the 6-month intervention period. Fixed and per-patient intervention costs will be calculated from PHH records. The monthly per-patient costs of health care services and out-of-pocket costs will be combined, and multivariate analyses comparing this sum (potential cost offset) for intervention versus usual care patients will be conducted.

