The second strategy is delivering targeted interventions (per established protocols) to patients identified as “high risk” by the CareSage predictive algorithm. Interventions will be adapted to fit the patient’s needs with a focus on the patient’s general functioning, including physical and psychological health status. Several studies have evaluated the effect of personalized multidisciplinary interventions for chronic conditions including heart failure, depression, and risk of falling in seniors [24,25]. Results showed significant reductions in health care utilization as well as improved patient quality of life. Therefore, we hope that an integrated approach to patient care management will have a significant impact on overall health care utilization and costs in older patients with multiple chronic diseases.

This study has a few limitations. First, the target population consists of English-speaking elderly patients who are receiving care from a home health care agency, thereby limiting the generalizability of the study results to other populations. The applicability of our study findings to other settings will require further investigation but, nevertheless, the findings will set the stage for future studies that could potentially target a more diverse population. Second, it might be difficult to capture data on hospitalizations that may occur outside of the Partners Healthcare network of hospitals. Capturing emergency department visits and hospitalizations outside of the Partners network is important because the study population is a high health care utilization group which is at risk for emergency transport and patients are typically taken to the nearest medical center for emergency care services. However, the Phillips Lifeline call center data and self-reported data from patients may help mitigate some of these challenges.

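### The only named source for 180-day mortality is the Partners databases, which may miss deaths outside the network, and no stated mitigation covers deaths

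*Protocol article*

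**What the plan says.** The 180-day mortality rate is a secondary outcome (Outcomes Measurement). It has its own planned comparison: "180-day mortality between the two study groups will be compared by using the Kaplan-Meier survival plots and the log-rank test" (Statistical Analysis Plan).

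Its source is fixed in Data Collection, where the list of utilization data ends with "avoidable admissions, mortality, and total medical expenditures) will be extracted from the Partners Healthcare patient databases", namely the Enterprise Data Warehouse and the Remote Patient Data Registry. The warehouse is described as a "single repository of clinical, operational, financial, and claims data of patients receiving care across the Partners system". The same section says "Data will be collected at enrollment and closeout as described in" an appendix that is not shown; the text at hand does not assign mortality to closeout. Lifeline data are assigned to emergency transport use.

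The limitations paragraph (Discussion, Study Rationale) says that "it might be difficult to capture data on hospitalizations that may occur outside of the Partners Healthcare network of hospitals". It extends this to emergency department visits, but does not mention deaths. As mitigation it offers that "the Phillips Lifeline call center data and self-reported data from patients may help mitigate some of these challenges".

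On contact during the intervention period, the Intervention section says of controls that "There will be no triage for control group participants", but also that "These participants will continue to use the PERS system". In the intervention arm, only patients flagged as high risk receive nurse calls.

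**The concern.** The article names one source for deaths and concedes that this source sees events outside the network poorly. The concession covers hospitalizations and emergency visits; for deaths the question is left open. Of the two mitigations, self-report cannot supply a patient's own death. Lifeline data are earmarked for emergency transport, and death is not among the example call outcomes given.

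Two things are at stake. First, missed deaths would make recorded mortality too low (survival curves too high) and would weaken a comparison that already rests on few events. Second, capture might not be equal. Patients stay on the home health service for 2-3 months on average, may enrol up to 3 months after discharge from it, and then pass through a 3-month observation period. Many may no longer be on service when the 180-day window opens. In that window flagged intervention patients have nurse contact that controls lack. If deaths learned that way enter the Partners records, the two arms would be measured differently.

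Mortality matters more here than its secondary rank suggests. The primary outcome counts fewer emergency visits as success, and mortality is the listed outcome that is neither utilization nor cost.

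**Working it through.** The article states no mortality rate and no capture rate, so there is no figure of the plan's own to reproduce. The only input taken from it is 185 participants per arm (Sample Size). Everything else below is assumed.

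**Expected deaths per arm**, 185 × assumed 180-day mortality:
- 3%: 185 × 0.03 = 5.6
- 5%: 185 × 0.05 = 9.3
- 10%: 185 × 0.10 = 18.5

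**Equal under-capture.** If both arms record a fraction s of deaths, recorded mortality is s × true mortality. The observed ratio is (s × p₁)/(s × p₂), so s cancels. With s = 0.80, a true 10% is recorded as 8%, and with no true effect the ratio stays at 1.00. The cost is power. For two proportions, two-sided alpha 0.05, n = 185 per arm:

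power = Φ{ [|p₂ − p₁| − 1.96 √(2p̄(1 − p̄)/n)] / √[(p₁(1 − p₁) + p₂(1 − p₂))/n] }

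Example at 5% v 10% with full capture: (0.05 − 1.96 × 0.0274)/0.0273 = −0.13, which gives 45%. With 80% capture the comparison becomes 4% v 8%: (0.04 − 1.96 × 0.0247)/0.0246 = −0.34, which gives 37%.

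| True control mortality | Power for true ratio 2, full capture | Same, 80% capture in both arms |
|---|---|---|
| 3% | 28% | 24% |
| 5% | 45% | 37% |
| 10% | 77% | 66% |

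**Unequal capture.** Observed ratio = true ratio × (capture in intervention / capture in control). With no true effect:

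| Intervention capture | Control capture | Gap (points) | Observed ratio |
|---|---|---|---|
| 90% | 80% | 10 | 0.90/0.80 = 1.13 |
| 95% | 75% | 20 | 0.95/0.75 = 1.27 |
| 90% | 70% | 20 | 0.90/0.70 = 1.29 |
| 100% | 70% | 30 | 1.00/0.70 = 1.43 |

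Read the other way, the true ratio that would be displayed as 1.00 is the reciprocal: 1/1.27 = 0.79 for the second row and 1/1.43 = 0.70 for the last. A real benefit of that size would vanish. Lower control capture always moves the observed ratio upward, so it cannot conceal harm.

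**Dilution.** Only flagged patients have nurse contact. If half of intervention deaths were captured at 95% and half at 75%, arm-level capture would be 85%, and the ratio 0.85/0.75 = 1.13, not 1.27.

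**Scale against chance.** At a true 10%, 95% v 75% capture gives 9.5% v 7.5% recorded, about 17.6 v 13.9 deaths. The standard error is √(2 × 0.085 × 0.915/185) = 0.029, so z = 0.02/0.029 = 0.7. Such a bias would distort the estimate, but on its own would not be expected to produce a significant result.

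**The case against.** The strongest reply is that the article does not say how vital status enters the databases. The warehouse holds claims as well as clinical data and may record some outside deaths. The same extraction applies to both arms, both keep the PERS device for 9 months, closeout collection is planned, and its schedule is in an appendix that is not shown. This stands far enough that one can say only that deaths may be missed. It does not remove the point: the article concedes the network gap with that same warehouse in use, and names nothing further for deaths.

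A reader might infer several stronger things that the document does not support:
- *Capture is lower in the control arm.* Not established. Nurse calls reach only flagged patients, education runs for 4 weeks, telemonitoring needs provider approval, and nothing says that deaths known to the nurse reach the Partners records.
- *Mortality is the only outcome that could show harm.* Readmissions and emergency transport use could also do so, and transport comes from Lifeline in both arms.
- *Patients with unknown status are counted as alive to day 180.* No censoring rule is given, and an article may leave that to the full plan.
- *The imbalance would hide harm.* The arithmetic shows the opposite direction.
- *Any under-capture invalidates the comparison.* Equal under-capture leaves the ratio unbiased and costs power.

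**Conclusion.** The point holds in limited form. The stated source for a secondary outcome with its own log-rank test may miss deaths outside the network, and neither the limitation nor its mitigations cover this. Equal under-capture would understate mortality and cost about 5 to 11 percentage points of power for a true ratio of 2 (assumed 80% capture, mortality 3-10%). Unequal capture is a plausible risk only. If control capture were 10 to 30 points lower, the observed ratio with no true effect would be about 1.1 to 1.4, seen as apparent harm or as a lost benefit. All capture and mortality rates are assumptions, and the true size cannot be found from the article. The primary outcome's sample size is not affected.

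**What to change.** Ascertain vital status, with date of death, at day 180 of the intervention period for every randomised participant, by identical steps in both arms. Combine:
- the Partners extract;
- the closeout contact;
- the notify contacts in the Lifeline database, where available and permitted;
- a public death-record search run for all participants, not only for those who could not be reached.

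Use this combined source for the mortality analysis. Censor at day 180 those confirmed alive or with no death found in the search. Keep last-known-alive censoring for those who could not be searched. Adding register deaths while censoring survivors at last contact would count deaths in full but cut survivor time, and so could inflate mortality.

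State the source in Data Collection and extend the limitations paragraph to deaths. The cost is a small amount of closeout and look-up work; no participants are added.

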### Analysis

#### Sample Size

Based on a similar study with a comparable population by Coleman et al, which reported an odds ratio of 0.57 for 180-day hospital visits compared to matched controls, we are expecting to reduce the number of emergency department visits within a 180-day period by at least 35% in the intervention group compared to controls [17]. At 80% power and a type I error (alpha) of .05, we will need 185 participants in each of the study arms, accounting for a lost to follow-up of 15%.

#### Randomization

A total of 370 participants will be enrolled and randomized (via a computer program) to one of two groups (intervention group or control group) in a ratio of 1:1 (185 participants per group). Randomization will utilize random permutated blocks to optimize balance in each treatment group at any point in time during the study. Treatment allocation will be concealed in an opaque envelop that will be opened after the informed consent procedures. Neither the patient nor the members of the study team will be aware of the treatment assignment until after randomization.

#### Statistical Analysis Plan

Data collected will be analyzed with data analysis (STATA, version 14) and statistical software (R, version 3.4.1). All the analyses will be conducted per the intention-to-treat principle. Descriptive statistics will be used to characterize the study sample, and we will summarize participants’ characteristics by study arm. The two study groups (intervention and control) will be compared by the Student *t*-test (two-tailed) for normally distributed and the Mann Whitney *U* test for skewed continuous variables, respectively. The chi-square test will be used for categorical variables. Time to event (readmission) and 180-day mortality between the two study groups will be compared by using the Kaplan-Meier survival plots and the log-rank test. Cox proportional hazard regression will be used to compute hazard ratio and compare outcomes between the two groups. We will also conduct subgroup analyses based on enrollment in iCMP during the 6-month intervention period. Fixed and per-patient intervention costs will be calculated from PHH records. The monthly per-patient costs of health care services and out-of-pocket costs will be combined, and multivariate analyses comparing this sum (potential cost offset) for intervention versus usual care patients will be conducted.

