**Methods:**

This is a two-arm randomized controlled trial recruiting 370 participants from a pool of high-risk patients receiving care at a home health agency. CareSage is a risk assessment system that utilizes both real-time data collected via a Personal Emergency Response Service and historical patient data collected from the electronic medical records. All patients will first be observed for 3 months (observation period) to allow the CareSage algorithm to calibrate based on patient data. During the next 6 months (intervention period), CareSage will use a predictive algorithm to classify patients in the intervention group as “high” or “low” risk for emergency transport every 30 days. All patients flagged as “high risk” by CareSage will receive nurse triage calls to assess their needs and personalized interventions including patient education, home visits, and tele-monitoring. The primary outcome is the number of 180-day emergency department visits. Secondary outcomes include the number of 90-day emergency department visits, total medical expenses, 180-day mortality rates, time to first readmission, total number of readmissions and avoidable readmissions, 30-, 90-, and 180-day readmission rates, as well as cost of intervention per patient. The two study groups will be compared using the Student *t* test (two-tailed) for normally distributed and Mann Whitney U test for skewed continuous variables, respectively. The chi-square test will be used for categorical variables. Time to event (readmission) and 180-day mortality between the two study groups will be compared by using the Kaplan-Meier survival plots and the log-rank test. Cox proportional hazard regression will be used to compute hazard ratio and compare outcomes between the two groups.

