### Outcomes Measurement

The number of 180-day (6-month intervention period) emergency department visits in the intervention and control group will be measured as the primary outcome of interest for this study. Secondary outcomes will include the number of 90-day emergency department visits, the total cost of intervention provided to patients, total medical expenditure incurred during the study period (including total expenses attributable to the avoidable admissions), 180-day mortality rate, and time to first readmission. Furthermore, health care usage including emergency transport use, readmissions (30-, 90-, and 180-day), and the total number of avoidable admissions will be evaluated at the end of the study period. Following the methodology cited in Walsh et al and Segal et al, potentially avoidable admissions will be determined by analyzing the principal diagnosis ICD-9 code associated with each inpatient admission and categorizing the codes into 3 groups which are (1) those potentially avoidable in both institutional and non-institutional settings, (2) those potentially avoidable only in institutional settings, and (3) those which are not determined to be potentially avoidable [7,15].

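### The only listed tests that fit the primary ED-visit count are the t test and Mann-Whitney U; a skewed count would go to Mann-Whitney, which does not estimate the targeted 35% reduction, and neither test uses observed time

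*Protocol article*

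**What the plan says.** Outcomes Measurement defines the endpoint as a count: "The number of 180-day (6-month intervention period) emergency department visits in the intervention and control group will be measured as the primary outcome". Sample Size states the aim on the same scale, to "reduce the number of emergency department visits within a 180-day period by at least 35% in the intervention group compared to controls", and the 185 per arm is described as "accounting for a lost to follow-up of 15" per cent.

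The Statistical Analysis Plan section gives a t test for normally distributed variables, then Mann-Whitney "test for skewed continuous variables, respectively. The chi-square test will be used for categorical variables". The abstract repeats the rule: "two-tailed) for normally distributed and Mann Whitney U test for skewed continuous variables, respectively". Kaplan-Meier, log-rank and Cox methods are introduced for time to readmission and mortality. Multivariate analysis is mentioned only for costs. All analyses are to follow intention to treat.

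No sentence pairs the primary outcome with a named test, so the reading here is by elimination. Among the listed methods, only the t test and Mann-Whitney can compare a visit count without first dichotomising it.

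**The concern.** Three things follow from applying this rule to a visit count.

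1. **Estimate.** Six-month ED visits per patient are usually few, with many zeros and a long right tail, so the rule would select Mann-Whitney. That test compares the ordering of patients, with heavy ties at zero. It does not estimate a ratio of visit numbers, so the main result would not address the 35% target.
2. **Power.** Ties and a long tail make Mann-Whitney less sensitive to a proportional reduction in the mean than a model for counts.
3. **Observed time.** The patients are aged 65 or older, 180-day mortality is itself an outcome, and 15% loss is expected. A raw count treats a patient who dies early as having few visits. If death or loss of capture differs by arm, the comparison of raw counts shifts even when the visit rate does not.

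The test is also chosen according to whether the data look normal, so the primary analysis is not fixed in advance.

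**Working it through.** **The plan's own figure.** Sample Size says "At 80% power and a type I error (alpha) of .05, we will need 185 participants in each of the study arms". Removing the 15% allowance, 185 × 0.85 = 157 evaluable per arm. No control mean, SD or event proportion is given, so 185 cannot be derived from the stated inputs. A two-sided comparison of two proportions with ratio 0.65 gives 158 / 0.85 = 186 per arm at an assumed control proportion of 43%, or 157 / 0.85 = 185 at 45.5% with continuity correction. The source effect, "reported an odds ratio of 0.57 for 180-day hospital visits compared to matched controls", is also a binary-type measure. The documents therefore do not show that the trial was sized for a comparison of counts.

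**Count scale.** For negative binomial counts with control mean m and dispersion k (variance = mean + k × mean²), the number per arm before loss is

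n = (1.96 + 0.84)² × [1/m + 1/(0.65m) + 2k] / (ln 0.65)²

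- m = 1.0, k = 1: 7.849 × (1 + 1.538 + 2) / 0.1856 ≈ 192
- m = 0.5, k = 1: 300
- m = 1.5, k = 1: 157

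At a control mean of 1.0 or less with k = 1, 157 evaluable patients leave no power to spare.

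**Power of the listed tests.** Simulated gamma-Poisson counts, true ratio 0.65, 185 per arm, 15% of patients with truncated follow-up, two-sided 0.05, 600 runs (Monte Carlo error about 2 points). The means and dispersions are assumptions. The count model used the true dispersion with robust standard errors, which favours it slightly.

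| Control mean | k | Mann-Whitney | t test | Negative binomial, time offset | Mann-Whitney deficit (points) |
|---|---|---|---|---|---|
| 0.4 | 0.5 | 51% | 58% | 58% | 7 |
| 0.6 | 1 | 52% | 60% | 62% | 10 |
| 0.6 | 2 | 40% | 51% | 53% | 13 |
| 1.0 | 0.5 | 78% | 85% | 87% | 9 |
| 1.0 | 1 | 60% | 71% | 73% | 13 |
| 1.0 | 2 | 42% | 56% | 59% | 17 |

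A separate run over means of 0.5 to 1.0 and k of 1 to 1.5 gave a deficit of 7 to 16 points. The t test is within about 3 points of the count model in every row.

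**Unequal observation.** Suppose there is no effect, 10% of controls and 25% of intervention patients are truncated, and truncation falls evenly over the period. Mean observed fractions are 1 − 0.10 × 0.5 = 0.95 and 1 − 0.25 × 0.5 = 0.875. The raw count ratio is then 0.875 / 0.95 = 0.92, an apparent benefit from missing time alone. In simulations of unequal truncation with no true effect, type I error was about 7 to 10% for the t test and 10% for Mann-Whitney, against 4 to 6% with a time offset. With the imbalance reversed and a true ratio of 0.65, the raw ratio moves to 0.65 × 0.95 / 0.875 = 0.71 and Mann-Whitney power fell to 41%. The truncation rates are illustrative; the protocol gives only the overall 15%.

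**Prior-visit covariate.** The gain depends on how stable each patient's visit rate is. When the simulation redrew the rate for half the patients between periods (157 per arm), power without and with the covariate was 75 and 75% (mean 1.0, k = 1), 63 and 64% (mean 1.0, k = 1.5), and 53 and 54% (mean 0.5, k = 1). With a fully stable rate the gain reached about 4 points in the 185-per-arm runs described above.

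**The case against.** The strongest reply is that this is a one-paragraph summary in a journal article. It names no test for the primary outcome, and covariates, offsets and partial follow-up are commonly left to an SAP. That stands as far as mere omissions go. It does not remove the point, because the section and the abstract both state a rule, and applied to a skewed count that rule yields a test without the estimate the trial needs.

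Several stronger readings are tempting, and the documents do not support them.

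- **That the t test also costs power.** It does not to any material degree; the loss belongs to Mann-Whitney.
- **That the planned analysis could say nothing about a 35% reduction.** Arm means reported with a t test give a ratio directly. The gap concerns Mann-Whitney and the lack of a pre-specified ratio with a confidence interval.
- **That the listed tests are invalid.** With equal follow-up they hold their type I error approximately. The distortion needs unequal observation between arms.
- **That anyone who leaves on day 20 counts as a success.** Data Collection takes ED visits from the Partners databases, so a patient who stops wearing the device may still have visits recorded. The problem applies to deaths and to patients whose care is no longer captured there.
- **That the 3-month observation count is a free baseline covariate.** Study Design randomizes at the start of that period, and allocation is opened at enrollment, so the count is collected after assignment is known.

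An offset also has limits. It does not remove bias from informative death; it changes the quantity to visits per day alive. It is undefined for a randomized patient with no intervention-period days.

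**Conclusion.** The point holds for a defined part of the plan. For a skewed visit count the stated rule leads to Mann-Whitney, which does not estimate the targeted reduction. It gives up about 7 to 16 points of power against an unadjusted count model, assuming control means of 0.5 to 1.0, dispersion of 1 to 1.5 and gamma-Poisson counts. Those figures are assumptions, so the direction is more secure than the size. Neither listed test uses observed time. This matters only if death or loss of capture differs by arm, and the illustrative 10% versus 25% case shows a shift of about 8% in the raw ratio. This is mainly a matter of efficiency and reporting, with a conditional threat to validity. It deserves correction before analysis because it governs the primary result and costs little.

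**What to change.** Name one primary analysis: a negative binomial (or Poisson with robust standard errors) regression of ED visits in the 180-day intervention period, with log(days alive and under database capture in that period) as offset. Report the rate ratio with 95% CI. Keep Mann-Whitney as a sensitivity analysis.

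Adjust for a prior ED-visit count taken from the same records before enrollment, not for the observation-period count. State how randomized patients with no intervention-period days are reported, so that the intention-to-treat statement remains accurate, and show deaths by arm beside the rate ratio.

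The cost is wording, plus an extraction of pre-enrollment visits and capture dates from databases already in use. Stata and R, both named, fit the model. The drawbacks are reliance on a model, a rate that must be read per day alive, and a covariate gain that may be small.
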